**Figure 1 F1:**
[figure not shown]
**Flowchart of the VITA-D study**.

### Randomization and blinding

If all inclusion and none of the exclusion criteria are met and informed consent has been obtained kidney transplant recipients will be included in the study and allocated a randomization number according to a randomization list. Thus, the participant will be randomly allocated to one of the two treatment arms. The random allocation sequence will be computer-generated using the Randomizer for Clinical Trials 1.7.0 developed at the Institute for Medical Informatics, Statistics and Documentation, Medical University of Graz, Austria. Block randomization will be used in order to prevent imbalanced treatment group sizes. We will use blocks of six to which the two treatment modalities will be randomly allocated in the ratio 1:1. To ensure homogenous treatment groups randomization is stratified by 25-hydroxyvitamin D_3 _levels, with one sub-stratum of kidney transplant recipients found to have 25-hydroxyvitamin D_3 _levels between 25 and 50 nmol per liter and another of kidney transplant recipients with 25-hydroxyvitamin D_3 _levels below 25 nmol per liter.

Participants, investigators, and outcome assessors will be blinded to the allocated treatment. Blinding will be ensured by the use of investigational products that are identical in packaging, labeling, appearance, smell, and taste. Unblinding will only occur in case of emergency and at the conclusion of the study. In most cases, however, discontinuing the treatment should be sufficient without the need for unblinding. Access to the randomization list is restricted to the pharmacist involved in the study and a research assistant.

### Study intervention

Kidney transplant recipients found to have 25-hydroxyvitamin D_3 _levels below 50 nmol per liter and who fulfill all of the inclusion and none of the exclusion criteria will be randomized to receive either oral cholecalciferol therapy (Oleovit^® ^D_3_-drops) or a placebo solution. Treatment starts on day five after kidney transplantation. Cholecalciferol will be administered at a dose of 6800 IU daily over a time period of one year.

The only adverse drug reaction caused by vitamin D_3 _that may occur is the rise in blood levels of calcium. In case of hypercalcemia the dose can be reduced immediately as serum calcium levels are monitored routinely at close intervals (daily within the postoperative hospitalization, i.e. between two and four weeks on average, thereafter weekly until the fourth month after transplantation, and subsequently every two to four weeks depending on post-transplant complications). At serum calcium levels > 2,65 mmol per liter vitamin D_3 _administration will be reduced to 3600 IU per day. If calcium levels persist above 2,85 mmol per liter over a period of four weeks vitamin D_3 _administration will be discontinued and restarted when serum calcium levels declined to ≤ 2,65 mmol per liter with only 3600 International Units per day. If calcium levels remain high this may be attributed to a persistent or transient hypercalcemia due to hyperparathyroidism as transient hypercalcemia is observed in 20–50% in kidney transplant recipients. Thus, the subject will be tested with ultrasound and ^99m^Tc-methoxyisobutyl isonitrile (MIBI) scan. However, these subjects will not be excluded from the study.

### Concomitant medication

Prior to kidney transplantation the administration of all active vitamin D supplements which are prescribed to almost all patients on dialysis will be discontinued.

Most kidney transplant recipients are administered a triple immunosuppressive therapy consisting of either mycophenolatmofetil or mycophenolat-natrium, tacrolimus, and prednisone. Steroid boli, monoclonal, and polyclonal antibodies are administered to treat acute rejection episodes.

### Study procedures

#### Day 0

Prior to transplantation patients will be recruited from the acute dialysis ward. There, and previous to kidney transplantation, blood samples will be taken of all kidney transplant candidates as a matter of routine, including a blood sample for 25-hydroxyvitamin D_3 _analyses.

#### Day 1–5

If a kidney transplant recipient is found to have 25-hydroxyvitamin D_3 _levels below 50 nmol per liter information about the VITA-D study, its purpose, putative benefits, and possible risks will be given to the patient and he/she will be invited to participate in the trial. All subjects will be informed that the participation in the trial is voluntary and that the subject may refuse to participate or withdraw from the trial at any time without giving reasons, without loss of benefits. Kidney transplant recipients who do not agree to participate in the study will receive standard care.

Demographic and baseline data will be collected of all participants within the first five days after transplantation (gender, age, body mass index, cause of end stage renal disease, mode of renal replacement therapy, duration on dialysis).

#### Day 5

Kidney transplant recipients who agreed to participate in the study will be randomized to receive either oral vitamin D_3 _therapy or placebo.

#### Treatment in hospital

Kidney transplant recipients are treated in hospital between two and four weeks on average. Within this time period blood samples are taken daily as a matter of routine, including analyses of serum creatinine, C-reactive protein levels and calcium levels.

The first DXA (dual energy X-ray absorptiometry) analysis will be performed within the first four weeks after transplantation depending on postoperative complications. However, we aim at performing it within the first two weeks.

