**Methods/Design:**

The VITA-D study, a randomized, placebo-controlled, double-blind study with two parallel groups including a total of 200 kidney transplant recipients, is designed to investigate the immunomodulatory and renoprotective effects of cholecalciferol (vitamin D_3_) within the transplant setting. Kidney transplant recipients found to have vitamin D deficiency defined as 25-hydroxyvitamin D_3 _< 50 nmol per liter will be randomly assigned to receive either oral cholecalciferol therapy or placebo and will be followed for one year. Cholecalciferol will be administered at a dose of 6800 International Units daily over a time period of one year.

The objective is to evaluate the influence of vitamin D_3 _substitution in vitamin D deficient kidney transplant recipients on the post-transplant outcome. As a primary endpoint glomerular filtration rate calculated with the MDRD formula (modification of diet in renal disease) one year after kidney transplantation will be evaluated. Incidence of acute rejection episodes, and the number and severity of infections (analyzed by means of C-reactive protein) within the first year after transplantation will be monitored as well. As a secondary endpoint the influence of vitamin D_3 _on bone mineral density within the first year post-transplant will be assessed. Three DXA analyses will be performed, one within the first four weeks post-transplant, one five months and one twelve months after kidney transplantation.

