## Methods

### Objectives

The proposed study is designed to evaluate whether cholecalciferol substitution in vitamin D deficient kidney transplant recipients has beneficial effects upon the post-transplant outcome compared to placebo. As a primary outcome we will evaluate the impact of cholecalciferol on

- graft function (analyzed using glomerular filtration rate calculated with the MDRD formula as well as albuminuria) one year after kidney transplantation

- the incidence of acute rejection episodes within the first year after kidney transplantation, and

- the frequency and severity (analyzed by means of C-reactive protein levels) of infections within the first year after kidney transplantation.

As a secondary objective we will assess whether cholecalciferol substitution influences the common decline of bone mineral density within the first year after kidney transplantation [44] analyzed by means of absolute bone mineral density (g/cm^2^).

Moreover, courses of calcium levels will be observed in order to assess the safety of cholecalciferol administration at 6800 International Units (IU).

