#### After 12 months

The third DXA analysis will be performed.

A summary of all study procedures is shown in Figure 2.

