### Statistical analysis

Baseline data will be expressed as mean values ± standard deviation for symmetrically distributed continuous variables, as median and 25th and 75th percentiles for asymmetrically distributed continuous variables, and as absolute and relative frequency for categorical variables.

Serum creatinine values after one year (the primary endpoint) will be compared between the groups by analysis of covariance (ANCOVA), taking into account as covariates creatinine value at randomization, 25-hydroxyvitamin D_3 _at baseline, and variables which, despite randomization, exhibit large group differences at baseline. ANCOVA will also be applied to the area under the curve of repeated measurements on serum creatinine, CRP, and bone mineral density during the first year of follow-up, using the same set of covariates. Categorical variables (number of acute rejection episodes and infections within the first year after transplantation) will be analyzed using χ^2^-test or fisher's exact test, as appropriate.

All analyses will be performed using an "efficacy subset analysis". Patients are included in this analysis if the study medication has been administered for more than seven days.

Moreover, courses of calcium levels will be described. Furthermore, the Bonferroni-Holm correction will be performed to preserve the global significance level of 5%.

Statistical analysis will be performed with SPSS.

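### The first bone scan may fall anywhere up to day 28 depending on complications, and the stated area-under-the-curve analysis of BMD makes no allowance for its date

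*Protocol article*

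**What the plan says.** All references are to the Protocol article.

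- **Start of treatment** (Study intervention): "Treatment starts on day five after kidney transplantation". Randomisation is on the same day (Study procedures, Day 5).
- **First DXA** (Treatment in hospital): it "will be performed within the first four weeks after transplantation depending on postoperative complications". The next sentence adds "However, we aim at performing it within the first two weeks". This is an aim, not a limit.
- **All three scans** (abstract, Methods/Design): "one within the first four weeks post-transplant, one five months and one twelve months after kidney transplantation".
- **Bone objective** (Objectives): secondary; whether treatment "influences the common decline of bone mineral density within the first year after kidney transplantation", measured as absolute density in g/cm².
- **Bone analysis** (Statistical analysis): "ANCOVA will also be applied to the area under the curve of repeated measurements on serum creatinine, CRP, and bone mineral density" over the first year of follow-up, with the covariates used for creatinine. Those are creatinine at randomisation, baseline 25-hydroxyvitamin D, and variables that happen to differ widely between groups at baseline. Neither the first BMD value nor the scan date is named.

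**The concern.** An area under absolute density is close to density multiplied by the time observed. Density changes by a few per cent over a year, so the length of the observed span has a strong influence on the area. With the last scan at 12 months and the first movable over several weeks, two patients with identical bone can get different areas because one was scanned later. The earlier-scanned patient has the larger area, which reads as better bone.

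The date is also not set purely by logistics, because the text ties it to postoperative complications. Most of the permitted window lies after randomisation, so the span can depend on events after treatment has begun. At stake is the precision of the bone comparison and, under one further condition, its fairness.

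**Working it through.** **The plan's own figure.** The only sample size is for creatinine: 2 × (0.5 × (1.960 + 0.842) / 0.2)² = 98.1, rounded up to 99 per arm. It reproduces and is not affected. The article gives no power figure for bone.

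**Gap between first dose and first scan.** At most 28 − 5 = 23 days; 14 − 5 = 9 days if the scan is done on the last day of the two-week aim. A scan before day 5 is also allowed.

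**Span from first to last scan**, taking 12 months as day 365:

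- first scan on day 14: 365 − 14 = 351 days
- first scan on day 28: 365 − 28 = 337 days
- ratio: 337/351 = 0.960, a fall of 4.0%
- per day of delay: 1/351 = about 0.28%

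**Area with bone loss included.** Trapezoidal area with scans at the first-scan day, day 152 (5 months) and day 365. Assumptions not in the documents: starting density 1.0 g/cm²; first-year loss of 2%, 5% or 8%, either linear or complete by month 5. Areas are in g/cm² × days.

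| Loss pattern | Area, day 14 | Area, day 28 | Change, raw area | Change, area ÷ span | Effect of halving the loss (raw area, day 14) |
|---|---|---|---|---|---|
| Linear 2% | 347.36 | 333.37 | −4.03% | −0.04% | +0.52% |
| Linear 5% | 341.89 | 327.93 | −4.08% | −0.10% | +1.33% |
| Linear 8% | 336.42 | 322.49 | −4.14% | −0.16% | +2.17% |
| By month 5, 2% | 345.23 | 331.27 | −4.04% | −0.06% | +0.84% |
| By month 5, 5% | 336.58 | 322.68 | −4.13% | −0.15% | +2.14% |
| By month 5, 8% | 327.93 | 314.09 | −4.22% | −0.24% | +3.52% |

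Within one patient, moving the first scan from day 14 to day 28 changes the raw area more than halving the bone loss does, in every row. Dividing by the span nearly removes this.

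**Effect on the comparison of arms.** Only a difference in mean scan date matters here. If the share of patients delayed from day 14 to day 28 differed by 10 percentage points, the mean date would differ by 0.10 × 14 = 1.4 days and the mean area by about 1.4 g/cm² × days. Halving the loss is worth 1.8 to 11.5 on that scale.

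**Effect on precision.** A uniform spread of first scans over days 5 to 28 has SD 23/√12 = 6.6 days, or 6.6/351 = 1.9% of the area. With an assumed between-patient SD of 10 to 15% and no adjustment for the first BMD value, the added variance is (1.9/15)² to (1.9/10)², about 2 to 4%. If the first value were adjusted for (assumed residual SD 2.5%), even a scan-day SD of 4 days (1.14% of the area) would add (1.14/2.5)² = 21%.

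**The case against.** The strongest reply is that the 4% belongs to one way of building the area. The article does not say where the curve starts or whether it is averaged over time. It refers only to the first year of follow-up, which could mean a common interval. Such detail is often left to a statistical analysis plan, and one that is not shown here may normalise the area. This stands as a limit: the size is conditional on a raw area starting at the patient's own first scan. It does not reach the scan window, which the article itself fixes and ties to complications.

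A reader might go further than the text allows in three ways.

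- *That the result is biased in favour of treatment.* Patients and staff are blinded, so mean scan dates can differ systematically only if a drug started on day 5 changes complications before day 28. The article does not define postoperative complications. Rejection and infection may be among them, and both are listed under the primary outcome, but nothing ties the scan date to bone itself. A 3-day difference in mean date would need about a 21-point difference in the share delayed (3/14).
- *That the first value is contaminated by treatment in most patients.* The article does not say how many are scanned after day 5. Even if all were, a 2% treatment gap at month 12 growing linearly (assumed) would be only about 0.05% after 9 days on drug and 0.13% after 23. Early loss missed by a late first scan is common to both arms unless timing differs between them.
- *That precision is badly damaged.* Under the covariates named, the added variance is small. It becomes material only once the first BMD value is adjusted for.

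A flexible window soon after transplant surgery is also a reasonable practical choice. That is a reason to handle its dates properly, not to leave them out of the analysis.

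**Conclusion.** The point holds as a weakness in how a secondary endpoint is measured and analysed. The first DXA may be taken up to 23 days after the first dose, on a date that can depend on complications, and the stated analysis variable is sensitive to that date. If the area is raw and starts at the first scan, a day-28 scan gives about 4% less area than a day-14 scan, against 0.5 to 3.5% for halving the bone loss under the assumed patterns. The established consequence is avoidable noise. Bias between arms is possible but conditional on an early treatment effect on complications, which the document does not establish. The primary endpoint and the sample size are untouched.

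**What to change.** In Statistical analysis, state that BMD is analysed on actual days since transplantation with a repeated-measures model, or that each patient's area is divided by its observed span. In either case adjust for the first BMD value. Make both changes together, because adjusting for the first value while keeping a raw area would leave scan-date noise as a larger part of what remains.

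In Treatment in hospital, make the existing two-week aim the target window and require the scan date to be recorded. Scans done later should be noted as deviations and kept in the analysis. An analysis restricted to patients scanned by day 14 is not advisable, because it would select patients on something that happens after randomisation.

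The cost is wording in two sections and one recorded date per scan, with no extra scan. If an unseen analysis plan already uses scan dates or a time-averaged area, only the window and the date recording remain to be settled. The small downside is that some patients with complications will be scanned outside the window.

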#### Outpatient treatment

After discharge kidney transplant recipients are seen once a week within the first four months after transplantation and are thereafter scheduled for visits every two to four weeks within the first year after transplantation. Blood samples are taken at every visit at the nephrological outpatient department.

#### Week 16

25-hydroxyvitamin D_3 _levels will be analyzed in order to check the response to treatment. In addition, eating habits and lifestyle (sun exposure, outdoor activities, and clothing) will be evaluated by means of a questionnaire.

#### After 5 months

The second DXA analysis will be performed.

#### After 12 months

The third DXA analysis will be performed.

A summary of all study procedures is shown in Figure 2.

**Figure 2 F2:**
[figure not shown]
**Study procedures**.

### Statistical analysis

Baseline data will be expressed as mean values ± standard deviation for symmetrically distributed continuous variables, as median and 25th and 75th percentiles for asymmetrically distributed continuous variables, and as absolute and relative frequency for categorical variables.

Serum creatinine values after one year (the primary endpoint) will be compared between the groups by analysis of covariance (ANCOVA), taking into account as covariates creatinine value at randomization, 25-hydroxyvitamin D_3 _at baseline, and variables which, despite randomization, exhibit large group differences at baseline. ANCOVA will also be applied to the area under the curve of repeated measurements on serum creatinine, CRP, and bone mineral density during the first year of follow-up, using the same set of covariates. Categorical variables (number of acute rejection episodes and infections within the first year after transplantation) will be analyzed using χ^2^-test or fisher's exact test, as appropriate.

All analyses will be performed using an "efficacy subset analysis". Patients are included in this analysis if the study medication has been administered for more than seven days.

Moreover, courses of calcium levels will be described. Furthermore, the Bonferroni-Holm correction will be performed to preserve the global significance level of 5%.

Statistical analysis will be performed with SPSS.

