### Study population and sample size

The study sample will consist of 200 kidney transplant recipients found to be vitamin D deficient (25-hydroxyvitamin D_3 _< 50 nmol per liter) with 100 subjects in each study group. Inclusion and exclusion criteria are detailed in the Appendix. The recruitment phase will last approximately four years with a follow-up period of one year for each subject. A flowchart of the VITA-D study is shown in Figure 1. The sample size calculation was performed according to the following assumptions: Based on the Vienna General Hospital database we concluded that the mean serum creatinine level one year after transplantation is x_1 _= 1,9 mg per deciliter with sigma, the common standard deviation, estimated to be σ = 0.5. An expert panel evaluated that a difference in serum creatinine levels of 0,2 mg per deciliter would represent a significant clinical improvement for the patient. Assuming that α = 0.05 and the power = 0.80 a sample size of 99 for each sample was calculated.

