### Interims analysis

An interims analysis will be performed after 6 months of follow-up for every subject. Within this analysis glomerular filtration rates between the two groups six months after transplantation and the incidence of acute rejection episodes within six months after transplantation will be analyzed. In case the interims analysis shows a significant difference between the two groups the study will be discontinued prematurely. The strict significance level of 0.001 for interim analysis requires no modification of the significance level for the main analysis [45]. The interims analysis will not break blinding.

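### The primary endpoint is named inconsistently (MDRD GFR, a list of outcomes, or serum creatinine), and the stated 80% power holds only if creatinine is the sole primary tested at two-sided 0.05.

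*Protocol article*

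**What the plan says.** Five places in the protocol article bear on the primary endpoint.

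- **Abstract, Methods/Design:** "As a primary endpoint glomerular filtration rate calculated with the MDRD formula (modification of diet in renal disease) one year after kidney transplantation". Rejection and infections are described only as also being monitored; bone mineral density is secondary.
- **Objectives:** the lead-in "As a primary outcome we will evaluate the impact of cholecalciferol on" introduces three bullets. The first is "graft function (analyzed using glomerular filtration rate calculated with the MDRD formula as well as albuminuria) one year after kidney transplantation", the second is acute rejection within the first year, and the third is "the frequency and severity (analyzed by means of C-reactive protein levels) of infections within the first year after kidney transplantation". No ranking or co-primary rule is given, and serum creatinine does not appear.
- **Study population and sample size:** the calculation is on serum creatinine at one year (mean 1.9 mg/dl, SD 0.5). "An expert panel evaluated that a difference in serum creatinine levels of 0,2 mg per deciliter" would be a clinically important improvement. With α = 0.05 and 80% power this gives 99 per arm, and 100 per arm are planned.
- **Statistical analysis:** "Serum creatinine values after one year (the primary endpoint) will be compared between the groups by analysis of covariance (ANCOVA", with creatinine at randomization and baseline 25-hydroxyvitamin D3 among the covariates. A Bonferroni-Holm correction is to hold the global level at 5%; the hypotheses it covers are not listed.
- **Interims analysis:** "Within this analysis glomerular filtration rates between the two groups six months after transplantation" are compared, together with acute rejection to six months, at a level of 0.001. A significant difference ends the study early.

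**The concern.** The article makes conflicting positive statements about which variable is primary. This is more than detail left to a fuller document: a full protocol or SAP could agree with only some of these sections.

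Two things are at stake.

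- **The scale of the primary test.** MDRD GFR is computed from creatinine, but by an inverse, non-linear formula that also uses patient characteristics. Means, SDs and p-values therefore differ between the scales, and a result near the boundary could be significant on one and not on the other. If the choice is still open at unblinding, the data could influence it.
- **The level at which that test is made.** If the Objectives' list is a set of co-equal primaries, the planned Holm correction applies among them, and the sample size was not calculated for that.

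**Working it through.** **Inputs.** Difference δ = 0.2 mg/dl, SD σ = 0.5 mg/dl, α = 0.05, power 0.80, 100 per arm planned (Study population and sample size); 1:1 allocation (Randomization and blinding). Sidedness is not stated.

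**Step 1: reproduce the plan's figure.** n per arm = 2(z₁₋α/₂ + z₀.₈₀)² σ²/δ² = 2(1.960 + 0.842)² × 0.25/0.04 = 98.1, rounded up to 99. This matches exactly. A one-sided test would give 78, so the plan's figure is two-sided.

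**Step 2: power for creatinine as sole primary at 100 per arm.** SE = 0.5 × √(2/100) = 0.0707, and δ/SE = 2.828. Power = Φ(2.828 − 1.960) = Φ(0.868) = 80.7%.

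**Step 3: power if the Objectives' outcomes are co-equal primaries under Holm.** Let creatinine stand in for the graft-function outcome. The strictest Holm step tests at 0.05/k, so power = Φ(2.828 − z₁₋₀.₀₂₅/ₖ). Three bullets give k = 3. Splitting either graft function (GFR, albuminuria) or infections (frequency, severity) gives k = 4, and splitting both gives k = 5.

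| k | α at first step | z | Power at 100 per arm | n per arm for 80% |
|---|---|---|---|---|
| 1 | 0.05 | 1.960 | 80.7% | 99 |
| 3 | 0.0167 | 2.394 | 66.8% | 131 |
| 4 | 0.0125 | 2.498 | 63.0% | 140 |
| 5 | 0.01 | 2.576 | 60.0% | 146 |

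These are worst-case values. Holm relaxes the level once other hypotheses are rejected, so the true power for creatinine lies between the row for k and 80.7%.

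**Step 4: GFR as sole primary.** The article gives no GFR mean, SD or target difference, so power cannot be derived from it. As an illustration only, assume creatinine means of 1.9 and 1.7 with SD 0.5, mean age 52, and GFR = 175 × creatinine^−1.154 × age^−0.203 with no sex term. The article does not print the formula, so its constants are also assumptions.

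| Assumed creatinine distribution | Age SD | GFR difference | GFR SD | Power at 100 per arm | n per arm for 80% |
|---|---|---|---|---|---|
| Lognormal | 0 | 6.51 | 14.38 | 89.2% | 77 |
| Lognormal | 13 | 6.56 | 14.74 | 88.3% | 80 |
| Normal, truncated above 0.6 | 0 | 5.97 | 17.07 | 69.6% | 129 |
| Normal, truncated above 0.6 | 13 | 6.04 | 17.42 | 68.9% | 131 |

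The same creatinine assumptions thus give about 69% to 89% on the GFR scale, depending on a distribution the article does not describe.

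**The case against.** The sample-size and Statistical analysis sections are the operative statistical text, and they agree on one-year creatinine, one target difference and one ANCOVA labelled primary. The Abstract also has a single primary endpoint, and that endpoint is derived from creatinine. On this view the dispute is mainly creatinine against its own transform, plus a loosely written list in the Objectives. That stands as a limit on the point, but it does not resolve the conflict: the article never says which section governs.

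A reader might infer more than the article supports:

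- **That no single test decides the trial.** This is too strong, because the two statistical sections, read together, do identify one.
- **That the chance of a false positive is about 23%** (1 − 0.95⁵ = 0.226 for five outcomes). This assumes uncorrected, independent tests. The plan applies Bonferroni-Holm at 5%, and the outcomes are unlikely to be independent, since GFR and albuminuria both measure graft function, and infection frequency and severity describe the same events. The defect is the unnamed family and its uncounted power cost.
- **That the trial has no power for GFR.** It states none, which is different. A creatinine difference implies a GFR difference.
- **That moving to GFR is free.** No new measurement is needed, but the expert panel judged a creatinine difference only, and 100 per arm may fall short of 80%.
- **That the missing albuminuria test is an error in itself.** An article may leave it to the full protocol.
- **That the interim defines yet another primary endpoint.** It sets its own comparisons at its own level and need not use the final variable, though the link should be explained.

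**Conclusion.** The point holds as an unreconciled inconsistency in the primary endpoint between the Abstract, the Objectives, and the two statistical sections, and it must be fixed. The stated 80% power is correct under one reading only: creatinine as sole primary at two-sided 0.05 (80.7% at 100 per arm). If the Objectives' list is taken as co-equal primaries, the strictest Holm step costs about 14 to 21 percentage points (80.7 − 66.8 = 13.9; 80.7 − 60.0 = 20.7). For GFR, the Abstract's endpoint, no power is stated.

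These figures assume the article's difference and SD, 100 evaluable patients per arm, and an unadjusted two-sample comparison. Adjustment for creatinine at randomization could raise all the creatinine figures, but the article gives no correlation from which to quantify this. The inconsistency does not depend on any of these assumptions.

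**What to change.** Before unblinding, name one primary endpoint and use it in every section.

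**Option that keeps the stated sample size and analysis:** serum creatinine at 12 months, by ANCOVA at two-sided 0.05. Correct the Abstract and Objectives to match; label GFR, albuminuria, rejection and infections secondary; and restrict Bonferroni-Holm to a listed secondary family. The cost is wording only.

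**If the sponsor keeps MDRD GFR:** change the sample-size and Statistical analysis sections to GFR, and state the target difference, the SD from the same hospital database, and the resulting power at 100 per arm. No new measurement is needed, but a clinically relevant GFR difference has to be agreed, and the sponsor must accept that power may fall below 80%.

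**If several co-equal primaries are really intended:** list the Holm family and re-size. On the creatinine assumptions, 80% power at the strictest step needs 131, 140 or 146 per arm for three, four or five hypotheses.

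In every case, Interims analysis should say how its six-month GFR and rejection comparisons relate to the chosen primary endpoint.

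### The primary ANCOVA picks its additional covariates by chance baseline imbalance rather than prognostic value, so the model cannot be fixed in advance and attainable precision is lost

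*Protocol article*

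**What the plan says.** The Statistical analysis section of the protocol article compares one-year serum creatinine between groups by ANCOVA. Two covariates are named: creatinine at randomisation, which is the baseline value of the outcome, and baseline 25-hydroxyvitamin D3, which is the stratification variable under Randomization and blinding. The model then also takes in "variables which, despite randomization, exhibit large group differences at baseline". The resulting set is reused for the ANCOVAs of area under the curve for creatinine, CRP and bone mineral density.

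Under Day 1–5, the article says "Demographic and baseline data will be collected of all participants within the first five days after transplantation". It lists six variables: age, gender, body mass index, cause of renal failure, type of renal replacement therapy and time on dialysis. Allocation is by stratified blocks "to which the two treatment modalities will be randomly allocated in the ratio 1:1".

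**The concern.** After proper randomisation, a difference between arms in a baseline variable outside the stratification is a chance event. Adjustment is useful in so far as the variable predicts one-year creatinine. The rule looks at the first property and ignores the second: it can bring in a non-prognostic variable that happens to differ, and leave out a strong predictor that happens to be balanced.

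Two things follow. First, the rule compares groups, so nobody can state the final primary model before the data are divided by group. Second, the standard error is not matched to the procedure. When a prognostic variable is omitted because it is balanced, the treatment estimate is in truth more precise than the model reports, so the test is conservative and power is lost. Because the set is shared, the same weakness reaches every ANCOVA in the plan.

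**Working it through.** **1. The plan's own sample size.** Inputs from Study population and sample size: difference 0.2 mg/dL ("a difference in serum creatinine levels of 0,2 mg per deciliter would represent a significant clinical improvement for the patient"), SD 0.5 ("the common standard deviation, estimated to be σ = 0.5"), α = 0.05, power 0.80. Sidedness is not stated.

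n per group = 2 × [0.5 × (1.960 + 0.842) / 0.2]² = 98.1, rounded up to 99. This reproduces the stated figure ("a sample size of 99 for each sample was calculated"); a one-sided test would need 78, so the calculation is two-sided. At the planned 100 per group, power is 80.7% (normal approximation) or 80.4% (t test). The SD is the raw one, with no reduction for covariates.

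**2. What prognostic covariates can add.** Power = Φ(0.2 / [0.5 × √(1 − R²) × √(2/100)] − 1.96), where R² is the share of outcome variance explained by all covariates:

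| R² | 0 | 0.1 | 0.2 | 0.3 | 0.4 |
|---|---|---|---|---|---|
| Power | 80.7% | 84.7% | 88.5% | 92.2% | 95.5% |

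**3. How often the rule would act.** Take six independent candidates, 100 per arm, no systematic differences.
- If large means p < 0.05: 1 − 0.95⁶ = 26.5% chance that at least one variable enters.
- If it means a standardised difference above 0.2: z = 0.2/√(2/100) = 1.41, two-sided probability 0.157, so 1 − 0.843⁶ = 64%.
- If above 0.1: z = 0.71, probability 0.480, so 1 − 0.520⁶ = 98%.

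**4. Simulation with six candidates.** Assumptions, none of them in the documents: two always-included covariates with joint R² 0.10; six independent normal candidates with joint R² 0.10 or 0.30; 100 per arm. There were 20,000 runs under the null and 8,000 at a true difference of 0.2 mg/dL.

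| Candidate R² | Rule | Type I error | Power |
|---|---|---|---|
| 0.10 | all six fixed in advance | 5.0% | 86.9% |
| 0.10 | imbalance p < 0.05 | 4.9% | 83.9% |
| 0.10 | difference > 0.2 SD | 4.5% | 84.2% |
| 0.10 | difference > 0.1 SD | 4.5% | 85.6% |
| 0.30 | all six fixed in advance | 5.0% | 94.4% |
| 0.30 | imbalance p < 0.05 | 4.3% | 84.9% |
| 0.30 | difference > 0.2 SD | 3.4% | 86.6% |
| 0.30 | difference > 0.1 SD | 3.3% | 90.7% |

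The power forgone is 1.3 to 3.0 points at candidate R² 0.10 and 3.7 to 9.5 points at 0.30. Ten candidates at R² 0.30 give a similar picture: type I error 3.1 to 4.0%, power 84.4 to 90.1% against 93.8%.

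**5. Simulation with three candidates,** the number that the fix would add. Assumptions: one fixed covariate with R² 0.10, cut-off 0.2 SD, effect 0.2/0.5 = 0.4 SD, 4,000 runs.

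| Correlation of each candidate with outcome | Fixed in advance | Imbalance rule | Gap (points) |
|---|---|---|---|
| 0.10 | 84.8% | 84.2% | 0.6 |
| 0.15 | 87.1% | 85.8% | 1.3 |
| 0.20 | 87.7% | 84.3% | 3.4 |
| 0.30 | 93.9% | 87.8% | 6.1 |

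A separate run gave gaps of 0.7, 2.8 and 6.3 points at correlations 0.1, 0.2 and 0.3.

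**6. If the cut-off is settled after results are seen.** Suppose the smallest p-value is taken from five models: no candidates, all candidates, and the three imbalance rules of step 4. Type I error is then 7.3% at candidate R² 0.10 and 8.5% at 0.30. With three candidates, choosing among cut-offs gave 5.1 to 5.9%.

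**The case against.** The strongest reply is that the model is mostly fixed already. The covariates with the clearest claim, the baseline outcome value and the stratification variable, are prespecified. A condensed article may also leave the candidate list, the cut-off and the timing to an analysis plan that is not shown. That stands: the absence of a cut-off is not itself a finding. It does not rescue the principle, because an analysis plan that defined large would still be selecting on imbalance.

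Four stronger readings are tempting, and the documents do not support them.
- *The choice is made after unblinding.* No time point is given. Coded groups, without outcome data, would be enough to apply the rule. What is certain is that it needs the group split.
- *The false-positive rate is inflated.* With a cut-off kept strictly, it is at or below 5%. Inflation needs the cut-off to be chosen with results in view, which the article does not propose.
- *The trial is underpowered as a result.* The sample size uses the raw SD, and every simulated version of the rule still gave about 84% or more.
- *The loss is larger than 10 points.* Five candidates each correlated 0.3 with the outcome would give 86% against 97%, but they would explain 5 × 0.3² = 45% of the variance. Nothing in the documents supports that figure.

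It is also fair to say that no document shows age, gender or time on dialysis predicting one-year creatinine once creatinine at randomisation is in the model. The gain from the fix could therefore lie near the bottom of the range.

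**Conclusion.** The point holds as a defect in a stated rule. Additional covariates are selected on chance imbalance, so the primary model, and the models that share its covariates, cannot be fixed before the data are split by group.

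The direction is firm: prespecified covariates gave higher power in every scenario run. The size is uncertain. Under the assumed correlations, type I error is about 3 to 5%, and the power forgone is about 1 to 6 points for three covariates and up to about 10 for six. Both depend on a covariate R² that the documents do not give, and on independent, normally distributed candidates, although some of the six listed variables are categorical. The loss is of attainable precision, not of the planned 80%. The change should be made, but the trial's validity does not hang on it.

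**What to change.** Delete the imbalance clause. Keep creatinine at randomisation and baseline 25-hydroxyvitamin D3. Add a short list of prognostic covariates, named now on clinical grounds and taken from data already collected in the first five days: for example age, gender and duration on dialysis. Report any model adjusted for an observed imbalance as a labelled sensitivity analysis.

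The cost is one sentence, written before any data are viewed by group, and about three degrees of freedom. With 200 patients the residual degrees of freedom go from 200 − 4 = 196 (intercept, treatment, two covariates) to 193. No new data, visits or patients are needed.

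If the full protocol or analysis plan already lists the covariates without reference to imbalance, it is enough to state that it supersedes this sentence.
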